# Unicompartmental knee arthroplasty vs. high tibial osteotomy for medial knee osteoarthritis (UNIKORN): a study protocol of a randomized controlled trial

**DOI:** 10.1186/s13063-023-07263-7

**Published:** 2023-04-05

**Keywords:** High tibial osteotomy, Unicompartmental knee arthroplasty, Intention to treat, Superiority trial, Knee osteoarthritis, Activity monitoring, Randomized controlled trial

## Abstract

**Background:**

Medial knee osteoarthritis (OA) is a common health problem resulting in knee pain and limiting patients’ physical activity. After failed conservative treatment, unicompartmental knee arthroplasty (UKA) and high tibial osteotomy (HTO) are possible surgical treatment options for this condition. There is a paucity of high-quality evidence in the literature comparing objective and subjective outcomes of these procedures. Also, there is no common agreement on whether these procedures provide comparable results in late-stage medial knee OA patients.

**Methods:**

We will perform a prospective randomized controlled trial comparing HTO and UKA in patients with late-stage medial knee OA. 100 patients with isolated medial knee OA (KL III–IV) are assigned to either UKA (*n* = 50) or HTO (*n* = 50) procedure in patients 45–65 years of age. Our primary outcome will be KOOS_5_ at one year postoperatively. Secondary outcomes include OARSI physical assessment, length of stay, wearable activity watch, radiographs (OA progression according to Kellgren-Lawrence classification), patient-reported outcomes (KOOS subscales, pain visual analog scale [VAS], Lysholm, and Oxford knee scores), and adverse events (conversion to total knee arthroplasty, surgery-related complications, need for revision surgery) outcomes. Our hypothesis is that neither of the interventions is superior as measured with KOOS_5_ at 12 months.

**Ethics and dissemination:**

The institutional review board of the Helsinki and Uusimaa Hospital District has approved the protocol. We will disseminate the findings through peer-reviewed publications.

**Trial registration:**

ClinicalTrials.gov/TooloH NCT05442242. Registered on 7/1/2022.

**Supplementary Information:**

The online version contains supplementary material available at 10.1186/s13063-023-07263-7.

## Introduction

Knee osteoarthritis (OA) is a common medical condition negatively affecting patients’ everyday lives and creating economic burden to societies [1–3]. Knee OA is often related to varus deformity and has various treatment options [4]. After failed nonsurgical care, total knee arthroplasty (TKA) has been the gold-standard treatment. Although TKA has proven superiority over nonsurgical care, [5] around 20% of patients are not satisfied with TKA [6–8]. In addition to TKA, unicompartmental knee arthroplasty (UKA) and high tibial osteotomy (HTO) are widely accepted treatment options in isolated unicompartmental OA [9]. Also, after failed UKA or HTO there is a possibility to convert to TKA.

In UKA, the damaged cartilage of the affected compartment is replaced by intra-articular implants. In a recent multicenter randomized controlled trial (RCT), UKA resulted in similar clinical outcomes and similar number of reoperations and complications compared with TKA. The cost-effectiveness of UKA was superior to TKA [10]. It has been estimated that 25–48% of knee OA patients would be suitable for UKA [4, 11]. However, the UKA rate has varied between 8 and 12.2% in different countries [12]. This suggests that UKA should be considered more often in patients with isolated medial compartment OA.

In HTO, the mechanical axis of the lower limb is corrected using an extra-articular osteotomy to shift weight towards the healthy lateral compartment in patients with medial knee OA and varus malalignment. The osteotomy can be performed with open or closed wedge technique [13]. While different complication profiles have been described, similar outcomes of these two methods have been reported [14]. Traditionally, HTO has been considered an option for younger active patients with a less severe OA. However, there is a paucity of high-quality evidence in the literature to support this assumption and in recent studies, HTO has been used in late-stage OA with good long-term results [15].

Recently, Jin et al. reported the first long-term follow-up results comparing HTO with UKA [16]. They found that WOMAC scores were superior in the UKA group but found no other significant differences between the groups in survival rates, complication rates, or OA progression. This study was performed using Propensity score matching (PSM) from a retrospective data.

To our knowledge, there are no previous RCTs comparing UKA with HTO in the treatment of late-stage medial knee OA. To fill this evidence gap, we designed this RCT to compare HTO and UKA in patients with medial late-stage OA of the knee with the following hypotheses.Null hypothesis is that there is no clinically significant difference between HTO and UKA in the primary outcome measure (The Knee Injury and Osteoarthritis Outcome Score composite, KOOS_5_) at 12 months postoperatively.There is no significant difference in rehabilitation time after surgery between HTO and UKA as measured with KOOS_5_ at follow-up timepoints.We expect no progression in lateral compartment OA in imaging studies during follow-up.

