## Methods and analyses

### Study setting

This study is a randomized controlled, pragmatic single-center, parallel-group, 1:1 superiority trial. Our goal is to compare the effect of HTO and UKA in patients with late-stage medial knee OA. The study will take place in Helsinki University Hospital. Approximately 50 UKAs and 50 HTOs are performed in our hospital every year.

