### Sample size

The sample size calculation was performed using G*Power 3.1 and was based on KOOS_5_ as the primary outcome measure in this trial. For the sample size calculation, we used a two-sided α level of 0.05. We assumed the MCID of the KOOS_5_ to be 10 points, [27, 31] with an SD of 15 points. Using these assumptions, the required sample size is 36 per group with 80% power to show a clinically important difference between the treatment methods with a two-sided type I error rate of 5%. With the assumption of 36% lost to follow-up, we decided to include 50 participants per group.

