### Statistical analyses

We will conduct all primary and secondary analyses according to the intention-to-treat principle. The Consolidated Standards of Reporting Trials statement will be used in the reporting of the trial results [32].

We will conduct the primary comparison (KOOS_5_ composite score) between the study groups using a mixed-model repeated-measures analysis of variance (MMRM ANOVA) allowing possible data missingness. We will assume data missing at random. Study group and time of assessment will be used as fixed factors and patients will be used as random factors. We are using the model to quantify the treatment effect as the absolute difference between the groups in KOOS_5_ (mean and 95% confidence interval [CI]) and *p*-value at 12 months postoperatively. A two-sided *p*-value of 0.05 will be used to indicate statistical significance.

We will compare secondary outcomes using a similar model where applicable (e.g., KOOS subscales, pain-VAS, Lysholm, Oxford knee score, OARSI). Radiological classification (KL- classification) is used for covariate in post hoc analysis. For categorical response variables, we will analyze the effects using the generalized estimating equations model with the unstructured correlation structure. Secondary outcomes will be considered explanatory and/or exploratory. Thus, multiplicity is not considered a problem. We will report adverse events descriptively.

We plan to perform a sensitivity analysis according to as-treated principle where the patients are analyzed according to their definitive treatment method irrespective of the randomization.

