### Expectations

We expect that KOOS scores improve significantly after operative treatment during the follow-up. We expect that there is no clinically relevant difference between HTO and UKA treatment in late-stage medial knee OA. Our results will provide high-quality evidence on the surgical treatment options for patients suffering from late-stage medial knee OA.

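### The written null is about clinical importance but the planned test is of zero difference, so a non-significant KOOS5 result alone cannot support the conclusion the protocol expects

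*Protocol article*

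**What the plan says.** Three places in the protocol article state or expect an absence of difference:

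- Introduction: "Null hypothesis is that there is no clinically significant difference between HTO and UKA in the primary outcome measure", at 12 months. The second hypothesis follows the same pattern: "There is no significant difference in rehabilitation time after surgery between HTO and UKA".
- Abstract, Methods: "Our hypothesis is that neither of the interventions is superior".
- Expectations: "We expect that there is no clinically relevant difference between HTO and UKA treatment in late-stage medial knee OA".

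The design and analysis are for superiority:

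- Study setting describes a "parallel-group, 1:1 superiority trial".
- Sample size: "we used a two-sided α level of 0.05", with a target difference of 10 points, SD 15 and 80% power, giving 36 per group.
- Statistical analyses: a mixed model gives the KOOS5 difference at 12 months with its 95% CI and p-value, and a two-sided p-value "of 0.05 will be used to indicate statistical significance".

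The Primary outcome measure section adopts an MCID of 10 points. Under Blinded data interpretation, the writing committee agrees on alternative readings of results labelled A and B before the code is broken. The article does not link the 95% CI to the 10-point MCID in either place.

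**The concern.** The written null and the tested null are different statements. The written one says that any difference is below a clinical threshold. The tested one says that the mean difference is exactly zero. The p-value therefore answers neither side of the written hypothesis. A small p-value shows a difference from zero, which may still be less than 10 points. A large p-value leaves open every value in the interval, which may include 10.

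The second case matters more here, because a non-significant result is what the investigators expect. Followed literally, the plan would then retain a null of no clinically significant difference on evidence that may be compatible with a difference of a full MCID in either direction. A reader choosing between two very different operations could take that as evidence that they give similar results.

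**Working it through.** **Inputs.** Target difference and MCID 10 points; SD 15; two-sided α 0.05; power 80%; 36 per group required; 50 per group recruited; 36% loss assumed (Primary outcome measure, Sample size). The evaluable number per group is taken as 50 (no loss), 36 (the required number) and 50 × (1 − 0.36) = 32 (the stated loss).

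**The plan's own figure.** n = 2 × (1.960 + 0.842)² × 15² / 10² = 35.3, so 36 per group. This reproduces the protocol's number. An exact t calculation gives 37, with 79.7% power at 36. The stated size is thus that of a superiority test of zero against a 10-point difference.

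**Precision.** SE = 15 × √(2/n). Half-width = t(0.975; 2n − 2) × SE. With an observed SD of 15, the interval lies inside ±10 only if the absolute observed difference is below 10 minus the half-width.

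| Evaluable per group | SE | t | Half-width | Largest observed difference with CI inside ±10 |
|---|---|---|---|---|
| 32 | 3.75 | 1.999 | 7.50 | 2.50 |
| 36 | 3.54 | 1.994 | 7.05 | 2.95 |
| 50 | 3.00 | 1.984 | 5.95 | 4.05 |

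At 36 per group, an observed difference between 2.95 and 7.05 points is non-significant and its interval reaches past 10. An observed difference of 7.05 sits at the significance threshold, with an interval from 0 to 14.1. Rejecting zero there says nothing firm about whether the difference exceeds 10.

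**Probabilities.** The chance that the CI lies inside ±10 was simulated with an estimated SD; the chance of p>0.05 is from the noncentral t distribution.

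| Evaluable per group | True difference 0: p>0.05 | True difference 0: CI inside ±10 | True difference 10: p>0.05 |
|---|---|---|---|
| 32 | 95% | 50% | 25% |
| 36 | 95% | 59% | 20% |
| 50 | 95% | 82% | 9% |

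So with no true difference at all, the share of non-significant results that fail to exclude a 10-point difference is about 48% at 32 per group, 38% at 36 and 14% at 50.

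**Sensitivity.** With SD 18, the chance of the CI lying inside ±10 at a true difference of 0 falls to 29% at 36 per group and 57% at 50. With a 90% CI and SD 15 it is 68%, 75% and 90% at 32, 36 and 50.

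**The case against.** The design itself is coherent: the superiority label, the sample size and the two-sided test agree with each other. A superiority trial may properly expect no difference, and the abstract's hypothesis can be read as the ordinary null put into words. The plan also goes beyond a p-value. It reports the difference with a 95% CI, names an MCID and has a blinded interpretation step. A detailed rule for reading the interval is often left to an analysis plan, which is not shown here. All of this stands, and the absence of such a rule is not by itself the fault. What remains is that the Introduction states a null that the planned test does not address. That is an error in the visible text.

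Three stronger readings are tempting and are not supported:

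- A reader might infer that the protocol will declare equivalence from p>0.05. No section says so. Expectations is a discussion paragraph, not a decision rule.
- A reader might quote only the figure of about 60%. That belongs to 36 evaluable patients per group, while 50 are to be recruited; with complete follow-up the figure is 82%.
- A reader might require the CI to lie wholly beyond 10 before calling a difference clinically important. At 36 per group the observed difference would have to exceed 10 + 7.05 = 17.05 points. If the true difference were the design value of 10, this would happen only 2.5% of the time, which defeats the stated purpose of the sample size. Reaching significance at about 0.7 of the target difference is normal for a trial with 80% power and is not a flaw.

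**Conclusion.** The point holds as a mismatch between the written hypothesis and the planned test. The p-value can neither refute nor support the null in the Introduction. The consequence is material for the result the investigators expect: even with a true difference of zero, the chance that the 95% CI excludes a 10-point difference is about 50% to 82% across 32 to 50 evaluable patients per group. A true 10-point difference would be missed in about 25% to 9% of trials over the same range. The wording creates a risk of over-reading a non-significant result; it does not show that the investigators intend to do so.

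These figures assume SD 15, a two-sample t interval and the MCID taken as the margin. The protocol sets no equivalence margin, and it plans to revisit the KOOS5 MCID later with an anchor question. The mixed model may give a somewhat smaller standard error; a larger SD would make matters worse.

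**What to change.** Restate the null in the Introduction as a mean KOOS5 difference of 0 at 12 months, and keep the superiority test. Fix the following reading in advance, for use in the blinded interpretation step:

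1. No clinically important difference is concluded only if the whole 95% CI lies within −10 to +10.
2. A non-significant result whose CI reaches beyond ±10 is reported as inconclusive on clinical importance.
3. A significant result is reported as a difference, with its estimate and CI discussed against 10 points. The CI need not lie wholly beyond 10.

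Bring the abstract hypothesis and the Expectations paragraph into line. If the chance of conclusion 1 is quoted, give the range for 32 to 50 evaluable per group (about 50% to 82% if the true difference is 0 and the SD is 15), not a single figure.

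The cost is wording. Patients, visits, sample size, model and estimates are unchanged. The downside is that some non-significant results must be reported as inconclusive.

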### Outcomes

The outcomes of this study consist of objective and patient-reported outcomes. The outcomes will be collected at randomization, preoperative visit, and postoperatively 3, 6, and 12 months. We will follow up the participants thereafter at 2, 5, and 10 years via letter survey.

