#### Primary outcome measure

The Knee Injury and Osteoarthritis Outcome Score (KOOS) is a validated patient-reported outcome measure (PROM) assessing the outcomes of various knee conditions [22]. The tool consists of five subscales: pain, other symptoms, activities of daily living, function in sports or recreational activities, and quality of life. We will use the KOOS_5_ composite score as the primary outcome measure. Based on clinical experience and literature, there will be only minimal change in pain and PROM scores after 1 year postoperatively [23]. Thus, the primary outcome measure, KOOS_5_ score for HTO vs. UKA is analyzed 12 months postoperatively. A minimal clinically important difference (MCID) of 10 points will be used [24].

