**Table 2 Tab2:**
[figure not shown]
Participant timeline of the trial

After the surgery, the days spent in the hospital will be recorded to follow the early recovery. Early readmissions within 90 days after surgery for any reason are reported for the analysis of possible complications. See safety considerations for the list of complications monitored.

The OA progression is monitored at the follow-up visits using radiographs of the knee at 3, 6, and 12 months after surgery, and the mechanical axis is re-evaluated at 12 months post-randomization. Patients not satisfied with the results of operative treatment (HTO or UKA) can be converted to TKA at any time during the follow-up.

For later determining the MCID of KOOS_5_ in this study, we will include an anchor question to the trial: “If you think about your pain level and daily activities this week, would it be acceptable that your knee would be like this for the rest of your life?”. The answer options are “Yes” or “No.” The proportion of patients reaching the Patient Acceptable Symptom State (PASS) be analyzed from the answers to this question.

We will use the Withings Move electronic watch as an activity tracker. The watches are given to patients right after randomization and the patients are asked to wear them for 24 h per day until the primary time-point of 12 months. The following data are recorded: ID number, date, time, number of steps per day, and sleeping hours. The watch is connected to a secured database and the data is wirelessly transferred and stored.

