**Secondary outcome measures**
1. KOOS subscales (pain, symptoms, activities of daily living, function in sports or recreational activities, and quality of life)
2. Average pain for the last 2 weeks (VAS 0–100 mm)
3. Lysholm and Oxford knee score
4. The 2013 OARSI recommended set of performance-based tests of physical function (i.e., 30-s chair stand test, 40-m fast-paced walk test, stair climb test, the timed up and go test, and 6-min walk test)
5. Days spent in hospital, readmission 90 days
6. Withings Move activity results
7. Radiographic progression of the arthrosis (KL grade mean) at 12 months
8. Changes in mechanical axis at 12 months (degrees from neutral axis)
9. Complications
10. Cost-effectiveness
11. Re-operation
12. Conversion to TKA

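### Hypothesis 2 is about rehabilitation time, but its stated measure, KOOS5 at visits from 3 months onward, compares score levels and cannot support a conclusion about duration

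*Protocol article*

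**What the plan says.** The Introduction lists three hypotheses. The second is: "There is no significant difference in rehabilitation time after surgery between HTO and UKA as measured with KOOS_5_ at follow-up timepoints".

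The Outcomes section gives the schedule: "The outcomes will be collected at randomization, preoperative visit, and postoperatively 3, 6, and 12 months". Later contacts are by post: "We will follow up the participants thereafter at 2, 5, and 10 years via letter survey". So KOOS5 is measured before surgery, and its first value after surgery is at 3 months.

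The Primary outcome measure section describes the instrument: "The tool consists of five subscales: pain, other symptoms, activities of daily living, function in sports or recreational activities, and quality of life". Statistical analyses sets out a repeated-measures mixed model with group and time as fixed factors. The effect it names is the between-group mean difference at 12 months.

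Two other measures bear on recovery. Under Secondary outcome measures, hospital days are recorded in order to follow early recovery, with readmissions within 90 days; both appear as item 5 of the secondary outcomes in Table 3. An activity watch is handed out right after randomization, and "the patients are asked to wear them for 24 h per day until the primary time-point of 12 months". On its content: "The following data are recorded: ID number, date, time, number of steps per day, and sleeping hours". Table 3 lists this as "Withings Move activity results". Neither measure is linked to hypothesis 2.

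**The concern.** The hypothesis names a duration and then fixes a level as its measure. Two arms can have the same mean score at 3 months after recoveries of quite different length, because the score says where patients are at that visit and not when they got there. The article states no recovery threshold that would convert scores into a time.

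Timing adds to this. If most recovery takes place before the first postoperative visit, the arms may have largely converged by the time they are compared. The hypothesis is worded as no difference, and the Expectations section anticipates no clinically relevant difference. A measure first taken late would tend to agree with that expectation whether or not it is true. At stake is a published statement that the two operations need equal rehabilitation time, resting on data that do not address it.

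**Working it through.** **1. Construct against measure**

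| Element | What the article fixes |
|---|---|
| Quantity in hypothesis 2 | Rehabilitation time, a duration |
| Stated measure | KOOS5 at follow-up visits, a five-subscale score |
| First postoperative value | 3 months |
| Named effect for KOOS5 | Mean difference at 12 months |
| Rule converting score to time | None in the text |
| Measure tied to early recovery | Hospital days; not linked to hypothesis 2 |
| Daily data across the gap | Dated step counts; not linked to hypothesis 2 |

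**2. The protocol's own figure**

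The inputs in Sample size are a difference of 10, SD 15, two-sided α 0.05 and 80% power. The normal approximation gives n = 2 × (1.960 + 0.842)² × 15² / 10² = 35.3, so 36 per group as stated. Noncentral-t power at 36 is 79.7%. The figure reproduces, and the SD of 15 is carried forward.

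**3. Precision of a KOOS5 comparison at one visit**

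Half-width of the 95% CI = t(0.975; 2n − 2) × 15 × √(2/n).

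- n = 50: 1.984 × 3.000 = 5.95
- n = 36: 1.994 × 3.536 = 7.05

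This treats the visit as a simple two-group comparison with SD 15. The mixed model may differ somewhat.

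**4. How much of a delay is left at 13 weeks**

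The documents give no recovery curve, so the following is assumed: gain(t) = 35 × (1 − exp(−t/τ)), with t and τ in weeks. Time to 90% recovery is τ × ln 10 = 2.303τ. The difference between arms at week t is 35 × [exp(−t/τ_slow) − exp(−t/τ_fast)].

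Worked example, τ = 3 and 5: time to 90% is 6.9 and 11.5 weeks, a gap of 4.6 weeks. At 13 weeks the difference is 35 × (0.0743 − 0.0131) = 2.1 points. At 26 weeks it is 0.2.

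| τ (weeks) | Gap in time to 90% (weeks) | Difference at 13 weeks | Difference at 26 weeks |
|---|---|---|---|
| 2 vs 4 | 4.6 | 1.3 | 0.1 |
| 3 vs 5 | 4.6 | 2.1 | 0.2 |
| 4 vs 6 | 4.6 | 2.7 | 0.4 |
| 3 vs 6 | 6.9 | 3.6 | 0.5 |
| 4 vs 8 | 9.2 | 5.5 | 1.3 |
| 5 vs 10 | 11.5 | 6.9 | 2.4 |

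All rows are below the protocol's 10-point MCID. All but the last are inside the 5.95 half-width; the last, 6.9, exceeds it and is just inside 7.05.

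**5. Wider assumptions**

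With gains of 30 to 40 points and half-times of 2 vs 4 up to 4 vs 8 weeks, the difference is about 3 to 9 points at 3 months, 0.3 to 4 at 6 months and under 0.5 at 12 months. Power with 36 per group is 12% to 69% at 3 months and 5% to 18% at 6 months. With 50 per group, the slowest and largest case (40 points, 4 vs 8 weeks) has 82% power at 3 months.

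**The case against.** The sentence supplies its own operational definition. Read whole, hypothesis 2 compares the course of KOOS5 over 3, 6 and 12 months, which fits a model with time as a factor. On that reading the fault is a loose phrase, and rewording cures it. This stands as far as it goes, and it is why rewording is the main fix. But the phrase is the one that would be carried into the conclusion, and the measure does not earn it.

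A reader might infer that the trial ignores early recovery altogether. It does not: hospital days are a duration, recorded for that purpose. They cover only the inpatient stay, however, and are not offered as evidence for hypothesis 2.

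A reader might also infer that any delay would be missed. That depends on fast assumed curves. Nothing in the article says recovery is nearly complete by 3 months; it says only that scores change little after 1 year. Slower curves leave differences that could be detected at the 3-month visit.

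Finally, one might want step counts to replace KOOS5 as the definition of rehabilitation. The Discussion gives a reasoned preference for what patients themselves report. No wear variable is listed among the recorded watch data, and conversion to TKA is possible at any time during follow-up. Preoperative steps in symptomatic patients who have just been given a training program are also an imperfect reference. These objections stand, so steps are proposed only as supportive. How the watch data are summarized is ordinary analysis-plan content, and the short entry in Table 3 is no defect in itself. An analysis plan, if one exists, could define a time endpoint, but only by departing from the measure that the hypothesis names.

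**Conclusion.** The concern holds in limited form. As worded, hypothesis 2 claims something about duration that KOOS5 at 3, 6 and 12 months cannot show, and a non-significant result would not support equal rehabilitation time. Under the assumed exponential curves with a 35-point gain and SD 15, delays of about 5 to 12 weeks leave about 1 to 7 points at 13 weeks against a half-width of 6.0 to 7.1. Such delays could often be missed, while slow, large ones may be found. Even a detected difference would be a gap in score and not a time. The mismatch itself does not depend on these curves; only its illustrated size does. The schedule is taken from the Outcomes text, since the timeline in Table 2 is not shown.

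The documents do not support extending this to the main result. Hypothesis 2 is not the primary hypothesis, secondary outcomes are declared explanatory or exploratory, and the 12-month KOOS5 comparison and its sample size do not rest on it.

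**What to change.** Reword hypothesis 2 as no difference between HTO and UKA in KOOS5 level at 3, 6 and 12 months, and state that no conclusion about rehabilitation time will be drawn from it.

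In addition, prespecify a supportive, exploratory analysis of the daily steps, reported alongside hospital days. One example is the time from surgery until the 7-day mean of daily steps regains the patient's own preoperative 7-day mean, censored at 12 months and compared between arms as time to event. State in advance how a day counts as worn, using the recorded data, so that an unworn watch is not read as inactivity. Also state how conversion to TKA is handled in the analysis.

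The cost is a change of wording in the protocol, the registry update that the article already promises for modifications, and one extra analysis of data already collected. No visit or measurement is added. The downside is that wear must be inferred, so some recovery dates will be uncertain, and the preoperative step level is an imperfect marker of full rehabilitation.
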